## 1. SUMMARY

### 1.1. TITLE

**Safety and Efficacy of Raltegravir + Darunavir/Ritonavir vs. Emtricitabine/Tenofovir + Darunavir/Ritonavir for Antiretroviral-Naïve Patients.**

### 1.2. INDICATION

**Raltegravir has recently been approved for the treatment of HIV-1 infection in treatment-experienced patients**

### 1.3. SUMMARY OF RATIONALE

HAART regimens with the most experience in demonstrating virologic and immunologic efficacy – and therefore recommended by the DHHS for initial therapy of antiretroviral naïve patients – are those composed of 2 NRTI and 1 NNRTI or PI with ritonavir boosting. However, because of concerns about long-term drug toxicity, the development of drug resistance, and potential complications in pregnant women, it is imperative that other drug combinations, including NRTI-free regimens, be investigated as possible alternative initial regimens.

Possessing a novel mechanism of action, Raltegravir has been found to have high efficacy and tolerability in combination with two nucleoside analogues in naïve patients, and with optimized background in highly experienced patients. Darunavir is the newest PI which has recently been shown to have excellent efficacy and tolerability in antiretroviral naïve patients. The combination of Raltegravir and a potent PI with an improved metabolic profile will likely yield an even better response among naïve patients, while preventing treatment-limiting toxicities.

### 1.4. SUMMARY OF STUDY DESIGN

This is a randomized, active control, safety/efficacy pilot estimation study. Eighty patients will be randomized 1:1 into two different treatment groups:

1. Group A: will receive Raltegravir + Ritonavir-boosted Darunavir
2. Group B: will receive Tenofovir + Emtricitabine + Ritonavir-boosted Darunavir

### 1.5. DOSAGE/DOSAGE FORM, ROUTE, AND DOSE REGIMEN

All study medications will be taken as recommended by manufacturer.

- a. Raltegravir: 400 mg twice daily, without regard to food. No recommendation for dosage adjustment in patients with severe renal impairment, mild or moderate hepatic dysfunction.
- b. Darunavir: 800 mg once daily plus ritonavir 100 mg once daily; administer with food. No recommendation for dosage adjustment in patients with severe renal impairment or end stage renal disease or severe hepatic dysfunction.
- c. Tenofovir: 300 mg once daily. No dosage adjustment required for hepatic impairment. Renal impairment:  $Cl_{cr}$  30-49 mL/minute: 300 mg every 48 hours;  $Cl_{cr}$  10-29 mL/minute: 300 mg twice weekly;  $Cl_{cr}$  <10 mL/minute without hemodialysis: No recommendation available; Hemodialysis: 300 mg every 7 days

## RADAR - Raltegravir And Darunavir Antiretroviral Regimen

- or after a total of 12 hours of dialysis (usually once weekly assuming 3 dialysis sessions lasting about 4 hours each)
- d. Emtricitabine: 200 mg once daily. No adjustment required for hepatic impairment. Renal impairment:  $Cl_{cr}$  30-49 mL/minute: 200 mg every 48 hours;  $Cl_{cr}$  15-29 mL/minute: 200 mg every 72 hours;  $Cl_{cr}$  <15 mL/minute (including hemodialysis patients): 200 mg every 96 hours; administer after dialysis on dialysis days

[figure not shown]

# RADAR - Raltegravir And Darunavir Antiretroviral Regimen

## 1.6. STUDY FLOW CHART

| TRIAL PERIOD                            |            | SCREENING |          |          |          | TREATMENT |           |           |           |           |     |
|-----------------------------------------|------------|-----------|----------|----------|----------|-----------|-----------|-----------|-----------|-----------|-----|
| Week*                                   | (-4 to -3) | 0         | 2        | 4        | 8        | 16        | 24        | 32        | 40        | 48        | EOT |
| Day                                     | (-28)      | 0         | (14+/-2) | (28+/-2) | (56+/-4) | (112+/-4) | (168+/-4) | (224+/-4) | (280+/-4) | (336+/-4) |     |
| Visit                                   | 1          | 2         | 3        | 4        | 5        | 6         | 7         | 8         | 9         | 10        | 11  |
| Informed Consent                        | X          |           |          |          |          |           |           |           |           |           |     |
| Medical History and Baseline Conditions | X          |           |          |          |          |           |           |           |           |           |     |
| Physical Examination                    | X          | X         | X        | X        | X        | X         | X         | X         | X         | X         | X   |
| Weight and BMI Calculation              | X          | X         |          |          | X        | X         | X         | X         | X         | X         | X   |
| Eligibility Criteria                    | X          | X         |          |          |          |           |           |           |           |           |     |
| CBC                                     | X          | X         | X        | X        | X        | X         | X         | X         | X         | X         | X   |
| Metabolic Profile                       | X          | X         | X        | X        | X        | X         | X         | X         | X         | X         | X   |
| Viral Load                              | X          | X         | X        | X        | X        | X         | X         | X         | X         | X         | X   |
| CD4+ and CD8+ Cell Counts               | X          | X         | X        | X        | X        | X         | X         | X         | X         | X         | X   |
| Fasting Blood Glucose                   | X          | X         | X        | X        | X        | X         | X         | X         | X         | X         | X   |
| Fasting Insulin Level                   | X          |           |          |          |          | X         |           | X         |           | X         | X   |
| Fasting Lipid Panel                     | X          | X         | X        | X        | X        | X         | X         | X         | X         | X         | X   |
| Urinalysis                              | X          | X         | X        | X        | X        | X         | X         | X         | X         | X         | X   |
| Lipoprotein Analysis                    | X          |           |          |          |          | X         |           | X         |           | X         | X   |
| LFTs                                    | X          | X         | X        | X        | X        | X         | X         | X         | X         | X         | X   |
| Hepatitis Serology                      | X          |           |          |          |          |           |           |           |           |           |     |
| HIV Genotyping                          | X          |           |          |          |          | X         |           |           |           |           |     |
| HIV Phenotyping                         | X          |           |          |          |          | X         |           |           |           |           |     |
| Adverse Events                          | X          | X         | X        | X        | X        | X         | X         | X         | X         | X         | X   |
| Obtain Plasma Sample for Storage        | X          | X         | X        | X        | X        | X         | X         | X         | X         | X         |     |
| Serum Pregnancy Test                    | X          | X         | X        | X        | X        | X         | X         | X         | X         | X         | X   |
| Randomization                           |            | X         |          |          |          |           |           |           |           |           |     |
| Dispense Darunavir/Raltegravir          |            | X         |          | X        | X        | X         | X         | X         | X         | X         |     |
| Concomitant Medications                 | X          | X         | X        | X        | X        | X         | X         | X         | X         | X         | X   |
| Adherence Questionnaire and Pill Count  |            |           |          | X        | X        | X         | X         | X         | X         | X         |     |
| Whole Body DEXA Scan                    |            | X         |          |          |          |           |           |           |           | X         |     |

## 2. CORE PROTOCOL

### 2.1 OBJECTIVES AND HYPOTHESES

#### 2.1.1 Hypotheses

We hypothesize that the virologic efficacy (time to loss of virologic response) at 24 weeks will be at least as high following a regimen of Raltegravir + boosted Darunavir as with a regimen of Tenofovir + Emtricitabine + boosted Darunavir.

We further hypothesize that a regimen of Raltegravir + boosted Darunavir will not result in higher rates of adverse events at 24 weeks than a regimen of Tenofovir + Emtricitabine + boosted Darunavir.

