### Secondary Outcome Measures:

- Percentage of patients with serious adverse experience
- Percentage of patients with drug-related adverse experiences that result in grade 3 or above laboratory toxicity
- Percentage of patients with drug related adverse experiences that lead to treatment interruption
- Time from treatment dispensation to the first development of a Grade 3 or 4 sign, symptom, or laboratory abnormality that is at least one grade higher than at baseline
- Percentage of patients with HIV viral load levels less than 50 copies/ml at 24 and 48 weeks.
- Median CD4 count at 24 and 48 weeks and at virologic failure
- Median change in limb fat by DEXA at week 48
- Percentage of patients with occurrence of fasting hypertriglyceridemia (TG >400) or hypercholesterolemia (TC >240) at week 48
- HIV-1 drug resistance patterns at baseline and at time of virologic failure

For assessment of safety and tolerability, counts and percentages of patients with clinical or laboratory adverse experiences of the following type will be tabulated (1) serious adverse experience, (2) drug-related adverse experiences that result in grade 3 or above laboratory toxicity; (3) drug related adverse experiences that lead to treatment interruption; (4) drug related adverse experiences leading to discontinuation.

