**IRB Approved**

**06/24/13**

[figure not shown]

Logistic regression analysis will be used to analyze outcome data to determine the difference between the two regimens. With 40 patients enrolled in each arm, the study has 80% power to rule out a 15% difference in efficacy between the two regimens. This assumes a true response rate of 85% for both treatment groups.

For assessment of safety and tolerability, counts and percentages of patients with clinical or laboratory adverse experiences of the following type will be tabulated: (1) serious adverse experience; (2) drug-related adverse experiences that result in grade 3 or above laboratory toxicity; (3) drug related adverse experiences that lead to treatment interruption; (4) drug related adverse experiences leading to discontinuation.

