**IRB Approved**

**06/24/13**

[figure not shown]

Logistic regression analysis will be used to analyze outcome data to determine the difference between the two regimens. With 40 patients enrolled in each arm, the study has 80% power to rule out a 15% difference in efficacy between the two regimens. This assumes a true response rate of 85% for both treatment groups.

The reasons for failure at week 48 should be the primary reason for the earliest treatment failure. For any visit, subjects who have achieved confirmed virologic success (two consecutive visits with HIV viral load < 50 copies/mL) will be considered successes. All others should be classified into the other appropriate categories listed in Table 2. All events occurring in the window should be considered events for that visit.

All patients who take study medication will be included in the analysis of safety and tolerability. Only those adverse experiences that occur while on study therapy, or within 14 days after discontinuation of study therapy will be included in the analysis.

For assessment of safety and tolerability, counts and percentages of patients with clinical or laboratory adverse experiences of the following type will be tabulated (1) serious adverse experience, (2) drug-related adverse experiences that result in grade 3 or above laboratory toxicity; (3) drug related adverse experiences that lead to treatment interruption; (4) drug related adverse experiences leading to discontinuation.

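### The 24-week hypothesis of no higher adverse-event rates is paired with a safety table that gives no between-arm difference, no interval and no week-24 cut

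*Protocol*

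**What the plan says.** Protocol section 2.1.1 sets two hypotheses. The first concerns virologic efficacy at 24 weeks. The second is that the test regimen "will not result in higher rates of adverse events at 24 weeks than a regimen of Tenofovir + Emtricitabine + boosted Darunavir". It is directional, tied to week 24, and covers adverse events without restriction.

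The matching analysis appears in section 2.4 (after the secondary outcome measures), section 2.6 and section 3.4: "For assessment of safety and tolerability, counts and percentages of patients with clinical or laboratory adverse experiences of the following type will be tabulated". Four types follow: serious events; drug-related events resulting in grade 3 or higher laboratory toxicity; drug-related events leading to treatment interruption; and drug-related events leading to discontinuation. Sections 2.6 and 3.4 count events that occur on therapy or up to 14 days after stopping it.

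The secondary outcome measures in section 2.4 include percentages such as "Percentage of patients with serious adverse experience". They also include one outcome that is not a percentage: "Time from treatment dispensation to the first development of a Grade 3 or 4 sign, symptom, or laboratory abnormality". No method or time point is given for it.

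On design, section 1.4 says: "This is a randomized, active control, safety/efficacy pilot estimation study". It adds: "Eighty patients will be randomized 1:1 into two different treatment groups". Section 2.6 again calls the trial an estimation study.

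**The concern.** The hypothesis asks whether one rate exceeds another by week 24. To answer it, the analysis needs a comparison of the arms, a statement of how large an excess remains possible, and a count that stops at week 24. The stated analysis has none of these. It also narrows the events to four categories, three of them limited to events judged drug-related.

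Safety is in the trial's title and is one of its two hypotheses. If the table shows similar percentages, a reader of section 2.1.1 is invited to take the hypothesis as supported, with nothing to show how much harm the data still allow. At 40 per arm that allowance is large.

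**Working it through.** **1. Is there a safety figure in the plan to reproduce?** No. The protocol gives no adverse-event planning rate, acceptable excess or power. Its only power statement concerns efficacy: "With 40 patients enrolled in each arm, the study has 80% power to rule out a 15% difference in efficacy between the two regimens", with "This assumes a true response rate of 85% for both treatment groups". For completeness, SE = √(2 × 0.85 × 0.15 / 40) = 0.0798 and 0.15 / 0.0798 = 1.879. At one-sided 2.5%, power = Φ(1.879 − 1.960) = 47%; 80% is reached only at a one-sided level of about 15%. That is a separate matter, and nothing below depends on it. The 15 points cannot be borrowed as a safety margin.

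**2. Hypothesis against analysis.**

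| Element | Hypothesis (2.1.1) | Stated analysis (2.4, 2.6, 3.4) |
|---|---|---|
| Time | 24 weeks | On therapy plus 14 days, with visits to week 48 |
| Events | Adverse events, unrestricted | Four categories, three of them drug-related only |
| Comparison | Not higher than control | Counts and percentages by arm |
| Precision | None stated | None stated |

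The time-to-first Grade 3 or 4 outcome does not fill the gap, because no method, bound or week-24 cut is attached to it.

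**3. What excess remains possible if the two arms look identical?** Inputs: n = 40 per arm (sections 2.6 and 3.4); observed rates of 5%, 10% and 20% (assumptions).

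Wilson limits for one arm: [p + z²/(2n) ± z√(p(1−p)/n + z²/(4n²))] / (1 + z²/n), with z = 1.96. For equal observed rates p with Wilson limits l and u, the Newcombe upper limit for the difference is √[(u − p)² + (p − l)²].

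| Observed in each arm | Wilson l, u | Upper limit for the excess |
|---|---|---|
| 2/40 (5%) | 0.0138, 0.1650 | √(0.1150² + 0.0362²) = 0.121 |
| 4/40 (10%) | 0.0396, 0.2305 | √(0.1305² + 0.0604²) = 0.144 |
| 8/40 (20%) | 0.1050, 0.3476 | √(0.1476² + 0.0950²) = 0.176 |

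A perfectly balanced table therefore still allows an excess of about 12, 14 or 18 percentage points.

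**4. How would a true doubling appear?** This is an exact enumeration over two independent binomials with n = 40 each. The Fisher column assumes a two-sided 5% test, which the protocol does not state. The last column uses only the bare table.

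| True rates, control v test | Fisher test misses the excess | Test arm numerically higher in the table |
|---|---|---|
| 5% v 10% | 96% | 74% |
| 10% v 20% | 84% | 87% |
| 15% v 30% | 72% | 93% |
| 20% v 40% | 59% | 97% |
| 30% v 60% | 27.5% | over 99% |

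The bare table also misleads in the other direction: with equal true rates of 10%, the test arm looks higher about 43% of the time. Reading the sign of the difference is therefore not a usable rule either.

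**The case against.** **The stronger reading fails.** A reader might infer that, under this plan, a doubled event rate would usually pass as not higher. The documents do not support that. The high miss rates need a significance test, with a non-significant result read as no excess, and the protocol states neither. On the table it does describe, a doubling would show as numerically higher in about 74% to 97% of trials at control rates of 5% to 20%. Even with a Fisher test, most doublings from a control rate of 30% would be found (72.5% power).

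**The missing detail may sit elsewhere.** Intervals and data cuts often belong in a statistical analysis plan, which is not at hand. Adverse events are recorded at every visit (section 1.6), so a week-24 count can be produced. This stands as far as it goes: the absence of an interval would be a weak point alone. But an analysis plan would not change the wording of section 2.1.1, and what the protocol itself fixes does not match that hypothesis in time, events or comparison.

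**This is a pilot.** Safety is not the primary objective (section 2.1.2), and no secondary objective in section 2.1.3 is an adverse-event comparison. Descriptive safety tables are ordinary at this size. That argues against a safety margin or a larger trial, and neither is asked for. It also argues for wording the hypothesis as estimation.

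**Tabulation is not the only method named.** Sections 2.6 and 3.4 apply logistic regression to outcome data without expressly limiting it to efficacy. It stands beside the efficacy power statement, however, and the safety paragraph mentions only tabulation.

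**Conclusion.** The point holds as a mismatch. A directional 24-week hypothesis is answered by a descriptive table of selected categories over all time on therapy, with no estimate of the difference and no bound. Identical observed rates of 5%, 10% and 20% would leave excesses of up to about 12, 14 and 18 points possible, so a balanced table could not support the hypothesis. If a 5% Fisher test were used, a doubling from control rates of 5% to 15% would be missed 72% to 96% of the time.

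These figures rest on 40 patients per arm and on assumed event rates. They show how little the trial can exclude. They do not show that a real excess would go unseen under the plan as written. The point does not affect the efficacy analysis. It should be corrected because it changes what the trial can say about safety.

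**What to change.** - **Sections 2.6 and 3.4:** for each tabulated safety category, report the difference in proportions (test minus control) with a two-sided 95% confidence interval, for example Newcombe, counted to week 24 and again to week 48.
- **Section 2.1.1:** reword the second hypothesis as an aim to estimate the difference in adverse-event rates at 24 weeks, naming the categories meant. Add that with 40 per arm and equal observed rates of 5% to 20%, excesses of up to about 12 to 18 points cannot be excluded.
- **Interpretation:** state that the safety conclusion is given by the upper limit of the interval, and that the absence of a visible or significant excess will not be taken as evidence that rates are not higher.

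The cost is wording in three sections, an added column and a week-24 count in the safety tables. No new patients, visits or data are needed. The downside is that the safety claim becomes visibly weaker.

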#### 2.1.2 Primary Objective

The primary objective is to determine whether a regimen of Raltegravir + Ritonavir-boosted Darunavir achieves a comparable virologic efficacy (TLOVR) at 24 weeks to Tenofovir + Emtricitabine + Ritonavir-boosted Darunavir

#### 2.1.3 Secondary Objectives

- a. Determine whether Raltegravir + Ritonavir-boosted Darunavir at 48 weeks is associated with a median change in CD4 count from baseline comparable to Tenofovir + Emtricitabine + boosted Darunavir
- b. Compare the lipid profiles of patients receiving Raltegravir + Ritonavir-boosted Darunavir with those receiving Tenofovir + Emtricitabine + boosted Darunavir at week 48
- c. Determine changes in lipoprotein particles profile, as defined by their apolipoprotein composition and lipoprotein particle size distribution, (LDL subtypes 1 through 7 and HDL subtypes), in both treatment arm at weeks 16, 32 and 48.
- d. Determine any changes from baseline to week 48, in insulin resistance by homeostasis model assessment (HOMA-IR) derived from fasting plasma glucose and insulin levels
- e. Determine any changes in percent of body fat, lean body mass, and bone density on whole body DEXA scans between baseline and week 48.

## 2.2 SUBJECT/PATIENT INCLUSION CRITERIA

Inclusion Criteria:

- The patient has documented HIV-1 infection.
- The patient is at least 18 years of age.
- Antiretroviral naive, defined as 7 days or less of ARV treatment at any time prior to study entry.
- HIV viral load greater than 5,000 copies/ml prior to study entry.
- Willing to use acceptable forms of contraception
- Hepatitis B surface antigen (HBsAg) negative at study entry

## 2.3 SUBJECT/PATIENT EXCLUSION CRITERIA

**IRB Approved**

**06/24/13**

[figure not shown]

Exclusion Criteria:

- Patient is current participant in a Raltegravir trial or in trials involving any of the other study medications (Darunavir, Tenofovir or Emtricitabine)
- Immunomodulators (e.g., interleukins, interferons, cyclosporine), HIV vaccine, systemic cytotoxic chemotherapy, or investigational therapy within 30 days prior to study entry. Individuals receiving either stable physiologic glucocorticoid doses, corticosteroids for acute therapy for pneumocystis pneumonia, or a short course (2 weeks or less) of pharmacologic glucocorticoid therapy will not be excluded.
- Known allergy/sensitivity to study drugs or their formulations
- Patient has a condition (including but not limited to active alcohol or drug use) that, in the opinion of the investigator, may interfere with patient adherence or safety
- Patient with acute hepatitis due to any cause or clinically significant chronic liver disease (defined as Child-Pugh Class B or C; see table 3)
- Patient has severe renal insufficiency defined as a calculated creatinine clearance at time of screening <30 mL/min, base on Cockcroft/Gault equation which is as follows (and 0.85 X this value for females):
  - $CrCl \text{ (mL/min)} = [(140 - \text{Age}) \times \text{Weight (in Kg)}] / 72 \times \text{Serum Creatinine (mg/mL)}$
- Serious illness requiring systemic treatment or hospitalization. Patients who have completed therapy or are clinically stable on therapy for at least 7 days prior to study entry are not excluded.
- Known clinically relevant cardiac conduction system disease
- Patient requires or is anticipated to require any of the prohibited medications noted in the protocol
- Current imprisonment or involuntary incarceration for psychiatric or physical (e.g., infectious disease) illness
- Pregnancy and Breastfeeding. Women who become pregnant during the study will be required to permanently discontinue their study regimens.

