### 3.5 Drug Accountability

**Table 3:** Child-Pugh classification of severity of liver disease

| Parameter            | Points assigned |           |           |
|----------------------|-----------------|-----------|-----------|
|                      | 1               | 2         | 3         |
| Ascites              | Absent          | Slight    | Moderate  |
| Bilirubin, mg/dL     | <2              | 2-3       | >3        |
| Albumin, g/dL        | >3.5            | 2.8-3.5   | <2.8      |
| Prothrombin time     |                 |           |           |
| Seconds over control | <4              | 4-6       | >6        |
| INR                  | <1.7            | 1.7-2.3   | >2.3      |
| Encephalopathy       | None            | Grade 1-2 | Grade 3-4 |

Modified Child-Pugh classification of the severity of liver disease according to the degree of ascites, the plasma concentrations of bilirubin and albumin, the prothrombin time, and the degree of encephalopathy. A total score of 5-6 is considered grade A (well-compensated disease); 7-9 is grade B (significant functional compromise); and 10-15 is grade C (decompensated disease). These grades correlate with one- and two-year patient survival: grade A - 100 and 85 percent; grade B - 80 and 60 percent; and grade C - 45 and 35 percent.

[figure not shown]

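### The creatinine-clearance formula in the renal exclusion criterion prints serum creatinine in mg/mL, a factor of 100 off the scale of its own 30 mL/min cut-off

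*Protocol*

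**What the plan says.** Protocol section 2.3 (exclusion criteria) rules out severe renal insufficiency, set as a "calculated creatinine clearance at time of screening <30 mL/min, base on Cockcroft/Gault equation". It then prints that equation for sites to use. The numerator is 140 minus age, multiplied by weight in kg. This is followed by a division sign, 72, a multiplication sign, and "Serum Creatinine (mg/mL)". No bracket ties 72 and creatinine together. The text adds "0.85 X this value for females".

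No other part of the protocol text shown restates or corrects the formula.

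Three other places show the scale and units that the protocol works in:

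- Sections 1.5 and 2.4.2 print clearance bands for tenofovir and emtricitabine, for example "30-49 mL/minute: 300 mg every 48 hours". The lower bands are 10-29 and below 10 for tenofovir, and 15-29 and below 15 for emtricitabine.
- Table 3, under section 3.5, lists "Bilirubin, mg/dL".
- The HOMA-IR formula in section 3.2.3.4 takes fasting glucose in mg/dl.

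**The concern.** The formula is part of an eligibility rule, and in the text shown it is the only numeric renal criterion. Two sites enrol (section 3.4.1), so a clearance worked out from the protocol should come out the same at both and should mean something against 30 mL/min.

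In the printed unit it does not. One mg/dL is 0.01 mg/mL, so a creatinine value converted as the line asks is 100 times smaller than the mg/dL figure. Depending on how the line is read, the clearance comes out 100 times too high or close to zero. The criterion's purpose is to keep out patients with severely reduced renal function, and the rationale in section 3.1 itself asks for caution with tenofovir in renal failure.

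A second, lesser matter is the missing bracket. If the line is evaluated strictly left to right, creatinine multiplies instead of divides. The result then rises as creatinine rises, which runs against a criterion that excludes low values.

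**Working it through.** **Inputs from the protocol (section 2.3):** numerator (140 - age) x weight in kg; constant 72; creatinine in mg/mL; factor 0.85 for females; cut-off below 30 mL/min.

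**Assumed inputs:** the protocol gives no patient values. Two illustrative men are used, and then a grid. Unit conversion: 1 mg/dL = 0.01 mg/mL.

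**Man 1:** age 40, 70 kg, creatinine 1.0 mg/dL = 0.01 mg/mL. Common term: (140 - 40) x 70 / 72 = 97.22.

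**Man 2:** age 50, 70 kg, creatinine 3.0 mg/dL = 0.03 mg/mL. Common term: (140 - 50) x 70 / 72 = 87.5.

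| Reading | Man 1 (mL/min) | Man 2 (mL/min) |
|---|---|---|
| Denominator 72 x creatinine, in mg/dL | 97.22 / 1.0 = 97.2 | 87.5 / 3.0 = 29.2 |
| Denominator 72 x creatinine, in mg/mL (printed unit) | 97.22 / 0.01 = 9,722 | 87.5 / 0.03 = 2,917 |
| Left to right, in mg/mL (printed unit) | 97.22 x 0.01 = 0.97 | 87.5 x 0.03 = 2.6 |
| Left to right, in mg/dL (unit changed, bracket not supplied) | 97.22 x 1.0 = 97.2 | 87.5 x 3.0 = 262.5 |

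Only the second and third rows use the unit as printed. In the last row, man 1 looks right only because his creatinine is 1.0; man 2 shows the value moving the wrong way.

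**Where the 30 mL/min cut-off falls at age 40 and 70 kg:**

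- Denominator, mg/dL: 97.22 / 30 = 3.24 mg/dL.
- Denominator, mg/mL: 97.22 / 30 = 3.24 mg/mL = 324 mg/dL.
- Left to right, mg/mL: 30 / 97.22 = 0.309 mg/mL = 30.9 mg/dL.

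**Grid** (assumed: age 18 to 80, weight 40 to 150 kg, creatinine 0.4 to 10 mg/dL, both sexes):

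- Denominator, mg/mL: 283 to 63,542 mL/min; none below 30.
- Left to right, mg/mL: 0.11 to 25.4 mL/min; all below 30.
- Left to right, mg/dL: about 0.5% of grid points below 30, all at low creatinine.

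Outside the grid the left-to-right result is not absolute. At age 18 and 150 kg the common term is 122 x 150 / 72 = 254.2, so creatinine above 30 / 254.2 = 0.118 mg/mL = 11.8 mg/dL would pass.

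**Comparison with the protocol's own scale:** its clearance bands run from below 10 to 49 mL/min. Of the two denominator readings, only mg/dL gives values that this scale can sort.

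**The case against.** The strongest answer is that the equation is named. With the name, the female factor and the cut-off all stated, a coordinator using a standard calculator gets sensible values and never needs the printed line. The other serum values in the protocol are in mg/dL. If the local laboratory also reports creatinine in mg/dL (an assumption), staff who enter the reported figure and read the denominator in the usual way get 97.2 and 29.2 for the two example men. Results such as 9,722, or 0.97 in a healthy man, would also give themselves away. Further, the investigator may exclude a patient for any condition judged to affect safety, and screening includes a metabolic profile. All of this stands, and it limits the practical effect.

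The objection to the bracket also has force. Writing / 72 x creatinine for a denominator of 72 x creatinine is common shorthand, and the layout in the source PDF cannot be checked from the extracted text. The bracket is therefore an ambiguity and not an established error.

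Neither argument rescues the unit. Supplying the bracket still leaves the result 100 times too high.

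A reader might infer three stronger things that the document does not support:

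- That the screen necessarily excludes everyone or no one. This holds only if creatinine is actually entered in mg/mL. If mg/dL is entered left to right, the screen runs backwards instead.
- That patients were wrongly admitted or rejected. Nothing shows that any clearance was computed from the printed line.
- That the error carries into the dosing bands. Sections 1.5 and 2.4.2 do not cite this formula.

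**Conclusion.** The unit in the section 2.3 formula is wrong by a factor of 100 when set against the cut-off in the same criterion and the clearance bands elsewhere in the protocol. Entered as printed, with creatinine in the denominator, no patient in a realistic range falls below 30 mL/min. Evaluated left to right, practically every patient does. These statements rest on the assumed age, weight and creatinine ranges and on staff converting creatinine to mg/mL.

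The practical effect is probably small because the equation is named. The point is still worth correcting: the text offers the formula for use in a safety screen, and nothing else in the protocol text shown puts it right. The 30 mL/min cut-off and the 0.85 factor are not in question.

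**What to change.** Reconcile the printed line with the equation that the protocol names: [(140 - age) x weight in kg] / [72 x serum creatinine in mg/dL], with the 0.85 factor for females and the 30 mL/min cut-off unchanged. The bracket costs nothing and removes the left-to-right reading.

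Ask each site how clearance was calculated at screening. If any site worked from the printed line, recalculate those values from the age, weight and creatinine already collected. If the sites used a standard calculator, no recalculation is needed.

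The cost is a one-line correction and, at most, a short recalculation from existing data. No new procedure or visit is involved.
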